#### Data collection

Using a secure web-based data collection tool, the following information was collected: date of ICU admission, admission category (elective surgery, emergency surgery, and medical), primary admission diagnosis (nine categories), sex, age, BMI, daily use of MV/propofol therapy, and Apache II score on the day of admission. Attending physicians or allied healthcare professionals with expertise in nutrition practices (e.g., dietitians) also recorded daily protein intake and route of additional caloric intake (enteral nutrition, parenteral nutrition). For the first 11 days after ICU admission, the database contains information on protein and energy intake, as well as the number of days on which a patient received parenteral nutrition or oral feeding at any time.

Daily propofol-associated energy intake was also collected from the day of ICU admission (partial day) to a maximum of 11 additional days after admission. Information on the exact dose of propofol (administered via 1% or 2% solutions) was not available in the database. However, as propofol-associated energy intake is closely related to the dose of propofol, propofol-associated energy intake can be used as a surrogate parameter for this dose (1mL of a solution containing propofol contains 50mg of soybean oil, and 50mg of purified egg phosphatide, equivalent to 1.1kcal/mL).

Patients were followed in the hospital for a maximum of 60 days after ICU admission. We recorded the time to in-hospital death or discharge alive. Patients who remained alive in the hospital for more than 60 days were considered censored for both risks at that time.

#### Sample size considerations

The large number of patients in the database (more than 18,000 with an ICU LOS > 2 days) will be sufficient to support advanced, in-depth statistical analyses. In this subgroup, the 60-day hospital discharge alive rate is approximately 70%, resulting in more than 10,000 events (discharges).^(15)^ Considering the number of planned predictor parameters (confounders, see below), the events per predictor parameter ratio will be large enough to perform reliable complex statistical analyses.^(16)^

### Exposure variables

–Number of days with propofol therapy preceding transition day from one clinical state to another (numeric variable), irrespective of whether a patient had propofol on transition day or not (for definition of state transitions see Figure 1)–The cumulated amount of propofol-associated energy intake (kcal/kg) (numeric variable) preceding transition day, irrespective of whether a patient had propofol on transition day or not–The amount of daily propofol-associated energy intake (kcal/kg and day) on transition day (numeric variable)–The amount of daily propofol-associated energy intake (kcal/kg and day) (categorized variable) during different phases after ICU admission. The associations of daily propofol-associated energy intake with the outcome will be cumulated for the early phase (Days 0 - 4 after ICU admission) and the late phase (Days 5 - 11 after ICU admission).

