### Confounder variables

The list of confounder variables is presented in table 1. To account for heterogeneity across ICUs, all models will include random effects for each unit.

**Table 1 t1:** List of confounder variables. In addition to these variables, all models will contain a random intensive care unit variable

Variable	Time of recording
Number of days on oral nutrition	Days 0 - 2 post ICU admission
Number of days on parenteral nutrition	Days 0 - 2 post ICU admission
Number of days with protein intake > 1.2g/kg day	Days 0 - 2 post ICU admission
Year of therapy	Admission date
APACHE II score	ICU admission
Main admission diagnosis*	ICU admission
Admission category (surgical elective/emergency, medical)	ICU admission
Age	ICU admission
Sex	ICU admission
BMI	Pre-ICU admission
Baseline number of days under MV†	Days 0 - 2 post ICU admission
Number of days under MV before state transition‡	Days 0 - 11 post ICU admission

ICU – intensive care unit; APACHE - Acute Physiology and Chronic Health Evaluation; BMI - body mass index; MV - mechanical ventilation.

* Gastrointestinal, cardio-vascular, metabolic, neurologic, orthopedic/ trauma, renal, pulmonary, sepsis, other. Sepsis was the main admission diagnosis, if there was an infection-associated circulatory dysfunction requiring vasopressor therapy which dominated dysfunction of other organs;

† only used when analyzing the association of daily propofol-associated energy intake (categorized variable) with time-to-discharge alive/in-hospital death (cumulated for the early and late phase after intensive care unit admission);

‡ only used in multistate models

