### Overall design of the multistate models

We will use multistate models to assess the association between cumulated daily propofol-associated energy intake preceding state transition; propofol-associated energy intake on transition day, and number of days with propofol therapy preceding state transition, adjusted for the use of MV, and the subsequent risk for an inevitable state transition (Figure 1).^(21,22)^ We will analyze state transitions on a daily basis (days 0 to 11 after ICU admission), since the database contains information on propofol use and total propofol-associated energy intake on a given day. There are no data on state transitions occurring within 24 hours. Furthermore, transitions between propofol states have only been recorded up to 12 days after ICU admission. This is because propofol data recording stopped if a patient died or was discharged from the ICU, or if they had been in the ICU for more than 11 days. In line with this, for the multistate models, we will only consider outcomes (absorbing states: in-ICU death and discharge from the ICU alive) up to day 12 after ICU admission.

All analyses (multistate models and competing risks, see below) will be performed using the Piecewise Exponential Additive Mixed Model (PAMM). Like the Cox model, this model class is a multiplicative hazards model that estimates the hazard rate (or, more generally, the transition hazards) conditional on the covariates. Coefficient estimates can be interpreted in the same way as in the Cox model, e.g., using hazard ratios. We will use the PAMM rather than the Cox model because it explicitly estimates the baseline hazard and facilitates the estimation of nonlinear and time-varying effects, as well as the inclusion of time-dependent covariates (e.g., the number of previous days on MV). The general idea is to partition the observation period into short time intervals and estimate a constant hazard rate for each interval. This enables the model to capture varying hazard rates at different times after ICU admission, making it suitable for situations where the risk of state transition changes over time (e.g., after ICU admission). In the context of a multistate model, the hazard by piecewise exponential models becomes the transition hazard. Details can be found in the references.^(9,15,23-26)^

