Hazard ratios can be used to describe the association of covariates and exposures with each transition (e.g., from alive to death in the ICU). In multistate settings, separate hazards are estimated for each possible transition. These individual transition hazards are then combined to obtain the overall transition probabilities by calculating the empirical transition matrix. While hazard ratios describe the direct effect on the instantaneous risk of a transition (relative risk), transition probabilities depend on the hazards of all possible transitions (absolute risk). Together, these two quantities provide a comprehensive interpretation of the underlying processes.

A particular focus will be on the concomitant use of MV, which is one of the main reasons for propofol use in critically ill patients and therefore the most important confounder of propofol-associated outcomes. The time-dependent confounder MV is considered as a separate state^(27)^ in the multistate model (Figure 1). This has the advantage that the transitions to the absorbing states "ICU discharge alive" and "in-ICU-death", and thus the transition probabilities to these states, can be modelled separately, depending on the current time-dependent propofol status (yes or no), but also on the subject-specific history of MV treatment and propofol administration (number of days with propofol therapy, cumulated propofol-associated energy intake). As the model is conditional on propofol status at any given time, but the frequency of MV use may vary between subjects within each propofol state, it allows the association of propofol and MV status with outcomes to be disentangled.

Results for the association between the exposure variables preceding transition (number of days with propofol therapy, cumulated propofol-associated energy intake (kcal/kg), propofol-associated energy intake (kcal/kg day) on transition day), and transition risk will be presented as adjusted hazard ratios (with 95%CIs) and adjusted transition probabilities (with 95%CIs) depending on a specific day after ICU admission (Days 1 to 11).

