### Sensitivity analysis for the multistate models

If it is decided to withdraw established life-sustaining therapies (e.g., MV) based on the presumed wishes of the patient (e.g., communicated by a surrogate) or the instructions of an advance directive, sedation may be changed to drugs stronger than propofol (midazolam), and opioids (morphine, etc.) are added to analgo-sedate the patient. Death usually occurs one to two days after these therapeutic changes. Consequently, in these cases, the transition from propofol to no propofol would not indicate an improvement in clinical status (as it would otherwise). To account for this bias within the transition from the state "propofol: yes" to the state "propofol: no", we will re-classify the subsequent absorbing state "in-ICU death" into "palliative in-ICU death", if death occurs one or two days after the preceding state transition (time course of states # 1 - 7, Table 3), and into "non-palliative death" in all other time courses of states.

**Table 3 t3:** Survey of time courses of different daily states used to re-define the absorbing state "in-intensive care unit death" into "palliative in-intensive care unit death" (time course of states #1 to #9) and "non-palliative in-intensive care unit death" (all other time courses)

Time course of states #	State on day x minus n (n > 2)	State on day x minus 2	State on day x minus 1	Initial state (day x)	Absorbing state (day x plus 1)
1	Any	Any	"Propofol: yes" "MV: yes"	"Propofol: no" "MV: yes"	In-ICU death
2	Any	Any	"Propofol: yes" "MV: no"	"Propofol: no" "MV: no"	In-ICU death
3	Any	Any	"Propofol: yes" "MV: yes"	"Propofol: no" "MV: no"	In-ICU death
4	Any	"Propofol: yes" "MV: yes"	"Propofol: no" "MV: yes"	"Propofol: no" "MV: yes"	In-ICU death
5	Any	"Propofol: yes" "MV: no"	"Propofol: no" "MV: no"	"Propofol: no" "MV: no"	In-ICU death
6	Any	"Propofol: yes" "MV: yes"	"Propofol: no" "MV: yes"	"Propofol: no" "MV: no"	In-ICU death
7	Any	"Propofol: yes" "MV: yes"	"Propofol: no" "MV: no"	"Propofol: no" "MV: no"	In-ICU death
8	Any	Any	"Propofol: no" "MV: no"	"Propofol: yes" "MV: no"	In-ICU death
9	Any	"Propofol: no" "MV: no"	"Propofol: yes" "MV: no"	"Propofol: yes" "MV: no"	In-ICU death

MV - mechanical ventilation; ICU - intensive care unit.

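### In the multistate models the propofol-duration hazard ratio also carries time since propofol was stopped, because no covariate separates the two at a given ICU day

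*Protocol article*

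**What the plan says.** All places are in the protocol article.

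- *Exposure variables*: the duration exposure is "Number of days with propofol therapy preceding transition day from one clinical state to another (numeric variable"). It applies "irrespective of whether a patient had propofol on transition day or not (for definition of state transitions see Figure 1"), so it enters transitions both from the states with propofol and from those without.
- *Overall design of the multistate models*, time axis: "We will analyze state transitions on a daily basis (days 0 to 11 after ICU admission"). Adjusted hazard ratios and transition probabilities are presented "depending on a specific day after ICU admission (Days 1 to 11").
- Same section, propofol history: besides current propofol status, the history consists of "number of days with propofol therapy, cumulated propofol-associated energy intake".
- *Confounder variables*, Table 1: the only covariate updated over time in the multistate models is "Number of days under MV before state transition". The caption adds: "In addition to these variables, all models will contain a random intensive care unit variable". Time since the last propofol day, or since propofol began, is not listed.
- *Sensitivity analysis for the multistate models*: on sedation changed after a decision to withdraw life support, "Death usually occurs one to two days after these therapeutic changes". The same is said of propofol started in end-of-life care. In-ICU deaths one or two days after such a switch are relabelled as palliative (Tables 2 and 3).
- The competing-risk section plans a weighted cumulative exposure model with recency for daily energy intake, and its sensitivity analysis uses a two-day lag. Number of propofol days is not the exposure there; it only sets the lead time.

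**The concern.** Exposure, time axis, propofol history and adjustment set are all stated, so this is not detail left to a fuller plan. Together they fix a comparison at the same ICU day between patients with more and with fewer propofol days. Among patients now off propofol, those with more propofol days have, as a rule, stopped more recently. If a patient who has just stopped is less likely to leave the ICU, or more likely to die, than one who stopped a week ago, the model books that difference to duration.

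Duration is part of the purpose stated in the introduction, and the general aim is evidence on safe dosing and duration. The multistate models are the only place where it is analysed as an exposure. With more than 18,000 patients the intervals will be narrow, so a recency effect could be reported as a precise duration effect.

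**Working it through.** **1. Identity.** Let P be propofol days and F propofol-free days, counted from day 0 through ICU day d. Then P + F = d + 1. On day 10, a patient treated on days 0 to 2 has P = 3 and F = 8; one treated on days 0 to 8 has P = 9 and F = 2. Both sum to 11. For one unbroken spell from day 0, F is the time since stopping.

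**2. Consequence.** Write the planned log-hazard as a(d) + βP + other terms, with a(d) the baseline by day. Substituting P = d + 1 − F gives [a(d) + β(d + 1)] − βF. The baseline absorbs the bracket. The ratio per propofol day, exp(β), is therefore exactly the inverse of the ratio per propofol-free day, exp(−β). With some late starts and restarts simulated, the within-day correlation of P with time since stopping still ran from −0.96 (day 2) to −0.73 (day 11).

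**3. Null simulation.** The article gives no figure for this point and no hazards by day. Its only related figure is consistent: 18,000 × 0.70 = 12,600, against more than 10,000 discharges stated. Assumed inputs: 55% on propofol at day 0, daily stop probability 0.22, restart 0.05, daily death hazard 0.02, daily discharge hazard 0.08 off and 0.01 on propofol, days 0 to 11, events after day 2. Duration has no effect on any hazard. A piecewise-exponential model was fitted by current propofol state with a free day baseline, propofol days and MV days, then refitted with an indicator for the first two days after a stop (or start). Hazard ratio per propofol day, 150,000 simulated patients:

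| Transition | Assumed change in first 2 days | Planned covariates (95% CI) | With indicator (95% CI) |
|---|---|---|---|
| Death, off propofol | none | 0.999 (0.988–1.009) | 0.997 (0.985–1.009) |
| | ×2 | 1.107 (1.097–1.117) | 0.998 (0.988–1.010) |
| | ×3 | 1.182 (1.172–1.193) | 0.997 (0.987–1.008) |
| | ×5 | 1.295 (1.285–1.305) | 0.999 (0.989–1.008) |
| Discharge, off propofol | none | 0.999 (0.994–1.004) | 1.000 (0.994–1.006) |
| | ÷2 | 0.930 (0.925–0.935) | 0.999 (0.993–1.005) |
| | ÷3 | 0.905 (0.900–0.910) | 0.999 (0.993–1.006) |
| Death, on propofol | none | 1.005 (0.985–1.025) | 1.005 (0.982–1.029) |
| | ×2 after start | 0.902 (0.888–0.917) | 0.999 (0.979–1.019) |
| | ×3 after start | 0.849 (0.837–0.861) | 1.009 (0.991–1.027) |

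Over five propofol days, 1.182 compounds to 1.182^5 = 2.31. At 18,000 patients and ×3, the true null was rejected in all 100 runs; with no recency effect, in 5%.

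**4. Other inputs.** A second null simulation of 18,000 patients assumed daily discharge hazards of 0.05, 0.12 and 0.20 and death hazards of 0.03, 0.02 and 0.01 on day 1, day 2 and day 3 or later after the last propofol day. From the state with neither propofol nor MV, with MV days adjusted, it gave 0.91 (0.90–0.93) for discharge and 1.14 (1.07–1.21) for death. A milder gradient gave 0.95 and 1.03. Adding days since stopping to the first setting returned 1.00 and 0.96 (0.89–1.03). When the hazard depended only on time since MV ended, the MV-day term already removed the bias. A third, with its own assumed hazards, gave 1.09 to 1.22 for death and 0.89 to 0.93 for discharge.

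**5. Planned relabelling.** Table 3 changes the label of some deaths and leaves discharge transitions as they were. Relabelling every simulated death within two days of a stop, a simplification of courses 1 to 7, gave 0.827 to 0.835 per propofol day for non-palliative death, including 0.835 with no recency effect. Patients who have just stopped stay at risk but cannot have that event.

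**The case against.** The strongest reply has four parts.

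- *Recency is in the plan.* A reader might infer that no model in the article accounts for it. That is not supported: the primary competing-risk model includes recency, with a two-day lag as sensitivity analysis. The gap is confined to the multistate models.
- *The bias is conditional.* A reader might infer that the duration ratio must depart from 1, or that the models will show harm from longer therapy. The documents do not support this. With a flat hazard the ratio stays at about 1, and from the propofol states recency of starting pushes the death ratio below 1, which would look protective. The article ties death to a recent switch only for end-of-life decisions, and says that stopping otherwise indicates improvement. It says nothing about a low discharge hazard just after stopping. All multipliers are assumed.
- *Ventilation is handled.* MV is a state and prior MV days are a covariate. If recency matters only through the end of ventilation, little bias remains. This stands; the point needs a recency effect specific to propofol.
- *The remedy has limits.* For one spell from day 0, ICU day, duration and linear time since stopping are exactly dependent. In a first propofol run, days since the start is the duration itself. This also stands, and it restricts the form of the fix.

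What remains is the algebra, the absence of any recency covariate in these models, and a sensitivity analysis that does not address discharge.

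**Conclusion.** The point holds for the multistate duration analysis. From the propofol-free states, the hazard ratio per propofol day mixes duration with recency of stopping. Under assumed two- to threefold changes in the first two days after stopping, with MV days adjusted, a true ratio of 1 appears as about 1.1 to 1.2 for death and 0.89 to 0.93 for discharge. For death, the article's own account of palliative care supports the premise but not the size; for discharge, both are assumptions. With a flat hazard, or if only time since MV ended matters, there is little or no bias. From the propofol states the distortion of the death ratio would run downward. The research question and outcome sections place this analysis under the secondary question and outcomes, and the primary model does not share the problem, so it should be fixed but does not undermine the primary result.

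**What to change.** **From the propofol-free states**, in every transition model (death, discharge, and switches of propofol or MV): add a prespecified recency term, either an indicator for one to two days since the last propofol day or a smooth of days since stopping, plus a never-user indicator. Report the duration hazard ratio with and without it.

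**From the propofol states**: use only a restricted form, an indicator for the first one to two days after a start or restart later than day 0. State that duration cannot otherwise be separated from recency there.

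Do not present the Table 3 relabelling as the correction for this problem.

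**Cost**: variables derived from daily data already held, in a model class chosen partly because it takes time-dependent covariates. Intervals widen somewhat. On the log scale in the simulation, the width for death after stopping at ×3 rose from ln(1.193/1.172) = 0.0178 to ln(1.008/0.987) = 0.0211, a factor of 1.19. For death after starting at ×3 it rose from ln(0.861/0.837) = 0.0283 to ln(1.027/0.991) = 0.0357, a factor of 1.26. Identification then rests on late starters, restarts and the restricted form, which the report should say.

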### Research question

The average causal effect of propofol on the risk of in-hospital all-cause death has been demonstrated in previous clinical trials. Associations between propofol doses, timing, and responses, however, are unknown. The present study aims to fill this gap. The primary research question focuses on the association between defined levels of propofol-associated energy intake in the early and late phases following ICU admission and competing risks (time to discharge alive (being a surrogate of morbidity), and in-hospital death, respectively). The secondary research question centers on the association between preceding cumulated or daily propofol energy intake, or the number of days on propofol prior to transitioning from propofol to, e.g., death or being free of propofol the day after transitioning. These factors will be examined in terms of measured variables and transition probabilities, while accounting for bias from confounding by indication or palliative care. The general aim is to provide more evidence on safe propofol dosing and duration.

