### Sensitivity analyses accounting for palliative care bias/confounding by indication

To account for palliative care bias in the multistate models and analysis of time-to-discharge alive/in-hospital death, a sensitivity analysis is required concerning patients with an early death after termination or beginning of propofol therapy (< 48 hours after the last day of propofol therapy). Palliative care bias arises if physicians modify therapy not for medical reasons but because of end-of-life decisions. Several scenarios are possible (Table 2):

**Table 2 t2:** Survey of sensitivity analyses that account for bias relating to indications and palliative care

	Primary outcome	Secondary outcome		
Outcome measures	Time-to-discharge-alive/in-hospital death	Hazard of state transition		
Exposure variables	Categorized daily propofol-associated energy intake (kcal/kg and day)	Number of days with propofol therapy preceding transition day	Cumulated amount of PAEI (kcal/kg) before state transition (initial state: propofol "yes")	Amount of daily PAEI (kcal/kg and day) on transition day (initial state: propofol "yes")
Sensitivity analyses	Use of a lag time of two days after the last day of propofol therapy	Re-definition of the absorbing state "in-ICU death" into "palliative in-ICU death" (for time courses of different daily states #1 to #9, Table 3) and "non-palliative in-ICU death" (all other state time series)	Re-definition of the absorbing state "in-ICU death" into "palliative in-ICU death" (if [PAEI on transition day minus PAEI on the day before transition day]/PAEI on the day before transition day ≥ 100%) and "non-palliative in-ICU death" (all other changes)	Re-definition of the absorbing state "in-ICU death" into "palliative in-ICU death" (if PAEI on transition day > 4.5kcal/kg day) and "non-palliative in-ICU death" (all other intake)

PAEI - propofol-associated energy intake; ICU - intensive care unit.

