### Sensitivity analysis for the competing risk models used to analyze time-to-discharge alive/in-hospital death

When analyzing the cumulative association between propofol-associated energy intake and these outcomes, we will use a lag time of two days to minimize indication bias due to lower doses approaching discharge (or to higher doses before death). Consequently, the time window (defined by the lead time, see above) for which cumulated associations of propofol-associated energy intake with time-to-discharge alive/in-hospital death are calculated will be shortened by two days.

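### Multistate models: intake on the transition day is usually a partial-day total when propofol is stopped, so low intake will be associated with liberation from propofol even if dose has no effect

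*Protocol article*

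**What the plan says.** The Exposure variables section of the protocol article lists three numeric exposures for the multistate models. Two of them, days on propofol and cumulated intake, are counted before the transition day. The third is "The amount of daily propofol-associated energy intake (kcal/kg and day) on transition day (numeric variable"). Table 2 ties it to patients who are still in a propofol state: "Amount of daily PAEI (kcal/kg and day) on transition day (initial state: propofol 'yes".

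Table 3 sets out the daily sequence in two columns, "Initial state (day x") and "Absorbing state (day x plus 1"). The Research question section speaks of transitions "prior to transitioning from propofol to, e.g., death or being free of propofol the day after transitioning".

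The data are daily totals. The section on the overall design of the multistate models states: "There are no data on state transitions occurring within 24 hours". The Data collection section flags only the ICU admission day as partial.

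For the competing risk models, the plan recognises that intake changes as the event nears: "we will use a lag time of two days to minimize indication bias due to lower doses approaching discharge". The multistate models have no such lag. Their sensitivity analyses split in-ICU death into palliative and non-palliative death and do nothing else.

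**The concern.** If propofol is given on day x and not on day x+1, the infusion ended during day x or at its close. The day-x total then reflects the infusion rate multiplied by the hours infused. As an illustration, a patient at a rate of 4 kcal/kg per 24 hours who is stopped at noon has 4 × 12/24 = 2 kcal/kg recorded. An identical patient who continues has 4. The database holds no hours or rates, so a low dose cannot be told from a short infusion, and no confounder in Table 1 captures hours infused. The exposure is therefore partly produced by the transition it is meant to explain.

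The stated general aim is evidence on safe dosing and duration. A gradient in which lower daily intake goes with faster liberation could be read as such evidence when it reflects only the clock time of stopping.

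**Working it through.** **Which day is the transition day?** Table 2 requires propofol in the initial state. Table 3 puts the initial state on day x and the next state on day x+1. The Research question section places "being free of propofol the day after transitioning". Together these point to day x, the last propofol day.

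**The plan's own figures.** The article gives no figure for this exposure. Its one event count, more than 10,000 discharges, is consistent with 18,000 × 0.70 = 12,600, but concerns hospital discharge and is not used below.

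**Null simulation A.** All inputs are assumptions, since the documents give no stop times or daily transition risks:
- 40,000 patients followed to day 11, with intake independent of outcome.
- Constant full-day intake, uniform on 1.5 to 6 kcal/kg.
- Daily risks of stopping 20%, ICU discharge 5%, death 2%.
- Day x is partial for stopping and discharge, and full for death and for staying on propofol.
- Each transition is regressed on intake with a complementary log-log model.

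Hazard ratio (HR) per 1 kcal/kg on day x, where the true value is 1:

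| Assumed stop time | Stopping | ICU discharge | Death |
|---|---|---|---|
| Uniform over the day | 0.43 | 0.51 | 1.24 |
| Middle third | 0.30 | 0.37 | 1.26 |
| Last half | 0.60 | 0.63 | 1.15 |
| Last quarter | 0.79 | 0.79 | 1.07 |

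Repeat runs move these by about 0.02. With day x−1 intake, all three were 0.99 to 1.02. The death figure exceeds 1 because patients who stop or leave on day x sit in the comparison group with shortened totals.

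**Discharge depends on a further assumption.** Simulation A gives every discharged patient a partial day x. But discharge is the state on day x+1, and a patient may be sedated throughout day x and stopped on the morning of discharge. With stop time uniform, varying the share of discharged patients who have a full day x gives:

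| Share with full day x | Discharge HR |
|---|---|
| 0% | 0.51 |
| 50% | 0.80 |
| 75% | 0.96 |
| 100% | 1.20 |

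**Null simulation B**, with different assumptions: 10,000 patients; median intake 3 kcal/kg, log-SD 0.5 between and 0.25 within patients; daily stopping probability 0.1 to 0.3; daily death probability 0.03; Poisson model.
- Stopping: 0.44 to 0.62 with stop time uniform over the day, and 0.76 to 0.82 if at least half the day is infused.
- Death: 1.02 to 1.09 from the partial day alone, and 1.15 to 1.20 if 30% of deaths follow a doubled dose.
- With the previous day's intake: 0.99 to 1.01 for stopping and 0.99 to 1.03 for death.

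**Patient-days lost by lagging.** Under A's risks the daily chance of leaving the state is 0.20 + 0.05 + 0.02 = 0.27. The share of first days over 11 days is 0.27 / (1 − 0.73^11) = 0.27 / 0.969 = 0.279, or about 28%.

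**The case against.** **The definition is inferred.** Transition day is not defined in words, state transitions are referred to Figure 1 (not shown), and Table 3 does not use the term. One part of the text points the other way. The palliative rule speaks of death one or two days after the preceding transition. That fits time courses 1 and 4 only if the transition is dated to the first propofol-free day. This stands, and it is why the fix begins with a definition. It does not rescue the exposure: on that reading, intake is zero by definition for every move to propofol-no.

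**Discharge.** A reader might infer that low intake must also predict ICU discharge. The documents do not support that. They do not say whether propofol usually stops on day x or on the day of discharge, and the sign of the bias turns on this.

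**Death.** A reader might infer that the partial day creates a strong link between high intake and death. The effect is smaller than for liberation and depends on the assumptions. End-of-life dose increases are a separate source, which the plan anticipates in two sensitivity analyses. Those remain imperfect: splitting deaths at 4.5 kcal/kg on the transition day defines the outcome by the exposure. In simulation B this alone gave 0.73 to 0.91 for non-palliative death with no dose effect.

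**Reach.** The exposure serves secondary outcomes only. The other two multistate exposures already stop before the transition day, the primary competing risk analysis does not use this one, and the Limitations section acknowledges confounding by indication and the missing within-day information. All of this stands and limits the severity.

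**Lagging.** The near-null results for day x−1 are built in, because neither simulation includes weaning before the stop. Tapering over several days would still affect day x−1.

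**Conclusion.** The concern holds for liberation from propofol. On the best-supported reading, transition-day intake is shortened by the stop itself. The resulting HR with no dose effect is roughly 0.3 to 0.8 per kcal/kg; its size depends on assumed stop times and event rates, but it was below 1 in every scenario. For ICU discharge, neither size nor direction can be fixed from the documents. For death, the partial-day mechanism adds an upward bias of about 1.02 to 1.27, apart from end-of-life dose increases. It does not apply to changes in ventilation status while propofol continues. No multistate lag or sensitivity analysis addresses liberation or discharge. This should be corrected, but it is confined to one secondary exposure and does not undermine the primary analysis.

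**What to change.** 1. State in words which day the transition day is, and align the Exposure variables section, Tables 2 and 3 and the palliative-death rule with it.
2. In the multistate models, make intake on the day before the transition day (day x−1), in patients with propofol on both days, the main daily-intake exposure. This also matches the article's own description of daily intake as preceding the transition, in the Research question section and the multistate design section.
3. Report the day-x version only as a labelled comparison.
4. Add a two-day-lag sensitivity analysis, as already planned for the competing risk models, because one day does not remove weaning over several days.

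The work is one re-indexed covariate from data already held. The loss of information is not trivial. First propofol days no longer contribute to this exposure (about 28% of propofol patient-days under the assumed risks), and the population narrows to patients with at least two consecutive propofol days. Both should be stated. For x = 1, the lagged value comes from the admission day, which the article itself flags as partial, so its handling should also be specified.
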